### Frequency and plans for auditing trial conduct {23}

The trial Steering Committee, consisting of two laboratory researchers, will meet once a month to review how the trial is conducted.

Independent data monitoring is not considered as this is a low-risk intervention.

### Plans for communicating important protocol amendments to relevant parties (e.g., trial participants, ethical committees) {25}

The plans to communicate important protocol modifications will be registered for all relevant parties (REBEC (trial registries, Ethics Committee of the Federal University of São Carlos investigators, trial participants, journals, and financial support).

### Dissemination plans {31a}

The results will be communicated to scientific events, such as conferences, congresses, symposia, and social media. The data collected will be used for scientific purposes, always safeguarding their privacy before, during, and after the trial.

## Discussion

It is noteworthy that, as far as we know, this is the first study to show the effect of a low-cost, home-based physical rehabilitation associated with the educational and supervised program to improve physical capacity, dyspnea, and quality of life in patients with COPD. Previous studies [25, 26] have brought the importance and the concept in developing alternative rehabilitation programs; however, there are still no protocols that encompass accessibility (low cost), individualized, and weekly progressive prescription and which compare different supervision levels by the physiotherapist, in symptomatic patients with COPD.

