### Eligibility criteria {10}

The inclusion criteria are (i) age between 50 and 85 years, (ii) diagnosis of COPD, (iii) absence of exacerbation and stability of drug treatment in the last 4 weeks, (iv) absence of PRP in the last 6 months, (v) Modified Medical Research Council (mMRC) greater than or equal to two, and (vi) low exercise capacity verified by the results of 6-min step test and/or 6-min walk test (lower than 80% of predicted value)—lack of cognitive impairment with language deficiency that impairs understanding the verbal instructions.

The exclusion criteria are conditions that impair executing the proposed tests [12], such as unstable angina and myocardial infarction in previous months, arrhythmias, unstable blood pressure, and body-mass index greater than 35 kg/m^2^; malignant cancer treatment; orthopedic, rheumatic, neuromuscular, and visual problems that make it impossible to walk and/or go up and down stairs.

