### Outcomes {12}

The patient’s assessment will be conducted in a standard sequence, presented in Fig. 1 (Participant timeline) and Fig. 2 and the assessment will be conducted in two visits, with at least 7 days between them. The procedure will also be executed before and after PRP to verify the effects of the program.

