## Statistical methods

### Statistical methods for primary and secondary outcomes {20a}

Data entry will be managed by a blinded assessor (not involved in rehabilitation), and the data will be recorded in a documents clouds. All data will be analyzed by Statistical Package for the Social Sciences (SPSS) version 21.0. Two-way mixed effect ANOVA will be used to compare intergroup e intragroup (pre- and post-intervention) changes, considering significant a *p* value < 0.05.

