### Contribution and clinical applicability

The main contributions will be a more accessible alternative rehabilitation protocol for patients with COPD patients, which will also include individualized prescription; hence, more effective than previous protocols. Therefore, accessibility is a key point to expand rehabilitation opportunities so that more COPD patients can perform PRP in an alternative location, like at home, basic health unit, or community. We expected that the protocol could be adapted and applied in different situations, such as during the vacation period at University’s outpatient unit or in different populations, such as liver transplantation, chronic kidney disease, and others lung diseases.

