### Other important information about the study

It is also expected that not only will we verify the pre- and post-hospitalization effect, but will also consider the minimum clinically important difference in all applied tests; thus, further confirming the effect of the intervention. In addition, in the post-intervention reevaluation of IG patients, they will be asked about adherence to weekly exercise, and this information will be recorded in medical records. SG patients will also be asked weekly about the frequency of the exercises performed.

Additional information worth noting is that all patients will receive medical support while participating in the study and can be referred to evaluation and conduction at any time.

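### Only weekly supervision is randomised, so pre/post changes and MCIDs cannot establish the effect of the programme or of individualised prescription

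*Protocol article*

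**What the plan says.** **What is randomised.** Objectives {7} sets out a comparison of the programme with and without a weekly physiotherapist-supervised session. Sequence generation {16a} names two groups, instruction (IG) and supervised (SG). Under Action for randomized groups, both receive the same booklet and exercise at home; IG has one supervised session at the start and SG has one every week for 8 weeks. No group goes without the programme, and none receives a non-individualised version.

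**What is to be concluded.**
- Outcomes {12}: "The procedure will also be executed before and after PRP to verify the effects of the program".
- Statistical methods {20a}: "Two-way mixed effect ANOVA will be used to compare intergroup e intragroup (pre- and post-intervention) changes", at p < 0.05. Section {20b} repeats this for additional analyses.
- Other important information about the study: beyond a before-after effect, the trial "will also consider the minimum clinically important difference in all applied tests; thus, further confirming the effect of the intervention". (The sentence speaks of hospitalisation, but no hospitalisation is part of this trial; I read it as before and after the programme.)
- Discussion: "this is the first study to show the effect of a low-cost, home-based physical rehabilitation associated with the educational and supervised program", with physical capacity, dyspnoea and quality of life named as the targets.
- Contribution and clinical applicability: the protocol is one "which will also include individualized prescription; hence, more effective than previous protocols".

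**How patients enter and are measured.** Eligibility criteria {10} requires "low exercise capacity verified by the results of 6-min step test and/or 6-min walk test", below 80% of predicted, and an mMRC of at least 2. Outcomes {12} makes the 6MST the primary outcome, performed once. The 6MWT and mMRC are secondary; the 6MWT is performed twice and the better distance is used.

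**The concern.** A randomised trial gives a protected estimate of the contrast it randomises. Here that contrast is weekly supervision. Anything said about the programme itself rests on before-after change with no arm that did without it, and anything said about individualised prescription against earlier protocols rests on a comparison across studies.

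Before-after change is a weak basis in this trial. Patients are chosen because they score badly on the 6MST or 6MWT and on the mMRC, and those measures are then outcomes. No separate screening measurement is described, so the qualifying value appears to be the baseline value. The primary test is done once, so any learning between the first and second performance counts as gain.

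At stake is the trial's headline. If both arms improve similarly, the stated reading would allow a report that the programme works, even though the randomised comparison showed no benefit of supervision and nothing in the design tested the programme.

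**Working it through.** **1. Stated conclusions set against the design**

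| Conclusion the article intends | Comparison it needs | In the trial? |
|---|---|---|
| Weekly supervision adds benefit (Objectives {7}) | SG against IG | Yes, randomised |
| The programme has an effect (Outcomes {12}; Discussion; Other important information) | Programme against no programme | No |
| Individualised prescription beats earlier protocols (Contribution and clinical applicability) | Individualised against non-individualised | No |

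Only the first row is identified. This needs no arithmetic and is the core of the point.

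**2. How much regression to the mean could contribute**

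The documents give no figure for it. Assumptions: normal scores; one test with a single cut-off; a proportion P of those screened falls below it; test-retest reliability r; no true change. The expected rise in SD units is

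(1 − r) × φ(c) / P, where c is the normal quantile of P and φ the normal density.

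- P = 0.50: c = 0, φ(c)/P = 0.399/0.50 = 0.798.
  - r = 0.85: 0.15 × 0.798 = 0.12 SD
  - r = 0.90: 0.10 × 0.798 = 0.08 SD
  - r = 0.95: 0.05 × 0.798 = 0.04 SD
- P = 0.80: c = 0.842, φ(c)/P = 0.280/0.80 = 0.350.
  - r = 0.85: 0.15 × 0.350 = 0.05 SD
  - r = 0.95: 0.05 × 0.350 = 0.02 SD

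A simulation over a wider range (source mean 70 to 90% of predicted, SD 20 points, r = 0.70 to 0.95) gives 0.03 to 0.34 SD. Its upper end needs low reliability together with a source population mostly above the cut-off.

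In the same simulation, with half qualifying and 18 patients per arm (36/2, equal allocation assumed), the chance of a significant within-arm gain with no true effect is 11% at r = 0.90 and 7% at r = 0.95. A valid test gives 2.5% in that direction.

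These figures leave out learning and natural course, which the documents do not allow one to size. They also ignore the and/or entry rule: a patient who qualifies on the 6MWT alone is not selected directly on the 6MST, so the effect on the primary outcome would be smaller.

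**3. Illustration only: separate within-arm tests**

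Suppose someone compared the arms by asking which had a significant pre/post change, when both truly improve by the same standardised change dz. With p the power of the two-sided paired t-test in each arm, exactly one arm is significant with probability 2p(1 − p).

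| dz (assumed) | n = 18: p | exactly one | n = 25: p | exactly one |
|---|---|---|---|---|
| 0.2 | 0.12 | 22% | 0.16 | 27% |
| 0.5 | 0.52 | 50% | 0.67 | 44% |
| 0.8 | 0.89 | 19% | 0.97 | 6% |
| 1.0 | 0.98 | 4% | 0.998 | 0.5% |

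Here n = 25 is 50/2. A valid between-group test would be significant in 5% of such trials. The documents give no value of dz, and 0.5 at n = 18 is almost the worst case, since 2p(1 − p) peaks at p = 0.5.

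**The case against.** The case on the other side is substantial.

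- **The right contrast is already planned.** The objective is the supervision comparison, the framework is superiority, and a two-way mixed ANOVA contains the group-by-time interaction. A time factor is part of that model and is not a misuse. This stands: the between-group analysis is sound on this point.
- **Much of the wording is Discussion prose.** The opening sentence of the Discussion is a novelty claim, and the next sentence names different supervision levels as part of the novelty. That is fair for the Discussion, but Outcomes {12} and {20a} are Methods text, and Other important information says how results will be read.
- **The MCID reference is not specified.** The article does not say whether the MCID is set against each arm's change or the SG-IG difference. That also stands; the within-arm reading is the natural one from the sentence, but it is not stated.
- **Regression to the mean is small and equal in expectation across arms.** It stands that the primary contrast is not biased. It does not rescue before-after claims, which have no other arm to cancel it.
- **Selection does not touch every outcome.** It does not apply to the 1-minute sit-to-stand test, 10RM, SGRQ, CAT or activPAL. These still lack a comparison without the programme.

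A reader might infer from "compare intergroup e intragroup (pre- and post-intervention) changes" that supervision will be judged effective if SG changes significantly and IG does not. The documents do not support this: no section says a group difference will be drawn from separate within-arm tests. The discordance table above is therefore a caution and not a finding about the plan.

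**Conclusion.** The point holds in a limited form. The trial can estimate the added effect of weekly supervision. It cannot estimate the effect of the programme or of individualised prescription, yet the article states in several places that before-after change and MCIDs will verify or confirm such effects, and it expects superiority over protocols that are not compared. This follows from the design alone.

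The contribution of regression to the mean is modest: about 0.04 to 0.12 SD if half of those screened qualify and reliability is 0.85 to 0.95, about 0.02 to 0.05 SD if 80% qualify, and smaller again for patients entering on the other test. Both the proportion and the reliability are assumed. Learning on the single 6MST and natural course may add to this by unknown amounts.

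The planned between-group comparison is not affected. The correction should be made because it settles what the trial may conclude.

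**What to change.** 1. In Statistical methods {20a}, state that confirmatory conclusions rest on the group-by-time term, reported as the SG-IG difference in change with its 95% CI.
2. In Other important information about the study, state that the MCID is read against that difference and its CI.
3. Report within-arm changes as descriptive estimates with CIs, not as evidence that the programme works. Whether p-values accompany them is a matter of preference; their interpretation is not.
4. Reword Outcomes {12} (verifying programme effects), the Discussion (showing the effect), Contribution and clinical applicability (more effective than earlier protocols) and Other important information (confirming the effect), so that each refers to the effect of adding weekly supervision or is marked as descriptive.

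The cost is wording. No extra patients, visits or data are needed and the ANOVA stays as planned. The sponsor gives up programme-efficacy claims, which this design could not have supported.

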### Thus, the potential impact and significance of the study: impact and significance of the study

It is expected that a low-cost once a week supervised rehabilitation program complemented with home-based exercises will present positive results, especially on exercise capacity, which will make available a more expanded and effective PRP for patients with COPD.

### Contribution and clinical applicability

The main contributions will be a more accessible alternative rehabilitation protocol for patients with COPD patients, which will also include individualized prescription; hence, more effective than previous protocols. Therefore, accessibility is a key point to expand rehabilitation opportunities so that more COPD patients can perform PRP in an alternative location, like at home, basic health unit, or community. We expected that the protocol could be adapted and applied in different situations, such as during the vacation period at University’s outpatient unit or in different populations, such as liver transplantation, chronic kidney disease, and others lung diseases.

### Other important information about the study

It is also expected that not only will we verify the pre- and post-hospitalization effect, but will also consider the minimum clinically important difference in all applied tests; thus, further confirming the effect of the intervention. In addition, in the post-intervention reevaluation of IG patients, they will be asked about adherence to weekly exercise, and this information will be recorded in medical records. SG patients will also be asked weekly about the frequency of the exercises performed.

Additional information worth noting is that all patients will receive medical support while participating in the study and can be referred to evaluation and conduction at any time.

### Strengths and limitations of the study

A limitation refers to the absence of lower limbs strengthening justified by the focus of the protocol that is based on functional physical tests.

## Trial status

This is the first and definitive protocol version. The trial is registered at URL: http://www.ensaiosclinicos.gov.br/rg/RBR-533hht/ with Register Number UTN code U1111-1220-8245. The registration date and initial data is September 20, 2018; the actual status is ongoing; and June 2021 is the estimated conclusion date. Study completion is expected to be August 2021. The protocol is approved by the Research Ethics Committee of the Federal University of São Carlos (UFSCar) number 4.348.948, CAAE: 85901318.0.0000.5504.

The study protocol has been submitted before the end of the recruitment and before the last patient.

## Abbreviations

COPD: Chronic obstructive pulmonary disease
PRP: Pulmonary rehabilitation programs
UFSCar: Physical Therapy Laboratory of the Federal University of São Carlos
ReBec: Brazilian Clinical Trials Registry
6MWT: Six-minute walk test
SPIRIT: Standard Protocol Items: Recommendations for Interventional Trials
mMRC: Modified Medical Research Council
kg / m2: Kilograms/meters squared
6MST: Six-minute step test
1MST: One *minute sit to stand test*
SQRQ: Saint George Respiratory Questionnaire
CAT: COPD Assessment Test
PADL: Physical activity daily living
IG: Instruction group
SG: Supervised group
SPSS: Statistical Package for the Social Sciences
FAPESP: Fundação de Amparo à Pesquisa do Estado de São Paulo
CAPES: Coordenação de Aperfeiçoamento de Pessoal de Nível Superior
